### Statistical methods

The primary analysis of this trial will be conducted under the principle of intention-to-treat. Baseline characteristics of the patients included in each treatment group will be reported and tabulated to demonstrate group comparability. For the primary analysis, we will use a two-sided independent t-test to determine a mean difference and 95% CI between the OED at MRI on day 7 ± 1 of the two anakinra treatment groups combined and the standard care group. In an exploratory analysis, we will determine whether a difference in OED exists between the high dose and low dose anakinra group, again using a two-sided independent *t*-test.

Safety analyses will include all SAEs and AESIs up to 90 days after randomisation. To determine the safety profile of anakinra between the three treatment arms, we will compare the number of AESIs and urgent medical reasons for study withdrawal between the three treatment arms in 2 × 3 tables, tested by the Fisher exact probability test. To assess BBB disruption, difference in the K^trans^ between the three treatment groups will be analysed with ANOVA.

To determine the effect of anakinra on the time-dependent profile of serum inflammatory markers, we will use a linear mixed model to assess the effect of anakinra dosage on the area under the curve for these metabolites compared to standard care. The effect of the treatment on the distribution of the mRS at 90 ± 7 days will be analysed using ordinal logistic regression yielding common odds ratio’s with corresponding 95% CI. We will use a two-sided independent t-test to determine a mean difference and 95% CI between the Barthel Index of the two anakinra treatment groups combined versus the standard medical management group.

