### Randomisation

Participants will be randomised in the ratio of 1:1:1 via a secure web-based internet system (CastorEDC). Treatment allocation will be stratified for centre of participation, admission ICH volume (10–30 mL vs >30 mL as estimated with the ABC/2 method on non-contrast CT at admission) and renal function (estimated glomerular filtration rate (eGFR) 30–49 vs >50 mL/min/1.73 m^2^) to ensure balance in factors associated with development of PHO and anakinra plasma concentrations. Treatment allocation is not blinded to participants nor to study team members, compatible with the open-label treatment in the PROBE design. Instead, outcome assessment will be blinded for treatment allocation.

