### Sample size calculation

The OED is known to be independent of haematoma size, with a normal distribution. Based on the available preclinical and clinical data we assume an OED of 0.60 (SD 0.25) at day seven in the standard care group and estimate a reduction of OED from 0.60 to 0.40 (SD 0.25) in the anakinra treated group (high and low dose groups combined).^
30
^ With a group size ratio of 1:2 for control versus treatment, a power of 0.80, and an alpha of 0.05, a sample size of 19 patients in the control group, and of 39 in the intervention group is required. Assuming a 25% drop-out rate due to the severity of ICH, the final sample size is 25 patients for the control group and 50 patients for the intervention group, resulting in a total sample size of 75 patients for this trial.

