A potential limitation of our study is the relatively limited sample size. The high mortality rate after ICH might lead to a substantial drop-out of study participant that are not able to undergo a MRI examination at 7 ± 1 days. Although our sample size would allow for a 25% drop-out, this might be higher resulting in decreased statistical power. Moreover, the estimated effect size is based on preclinical data which might not translate to a human study. Using OED as our metric for PHO in our primary outcome analysis aims to mitigate the required sample size, as it is not affected by haematoma volume and thus strongly reduces the required sample size in comparison with using absolute or relative PHO.^
27
^

One other randomised phase II study has investigated anakinra to reduce PHO in patients with ICH (BLOC-ICH).^
23
^ In this placebo-controlled trial, patients with spontaneous supratentorial ICH were randomised to receive either 100 mg of anakinra subcutaneously twice daily during the 72 h after ICH onset, or placebo. Primary outcome was OED on CT imaging obtained at day 3 after symptom onset. Secondary outcomes included serum inflammation markers and functional outcome at 3 months. Patient recruitment was severely impacted by the COVID-19 pandemic and the trial had to be ceased prematurely after inclusion of 25 of the intended 80 participants. Although this trial provides preliminary data on the safety and feasibility of anakinra in acute ICH patients, it lacked statistical power to determine the effect of anakinra on perihaematomal oedema formation. We will collaborate with the investigators of BLOC-ICH to combine data into an individual patient data meta-analysis of patients treated with anakinra after ICH once the ACTION trial has been completed.

In conclusion, the ACTION trial has the potential to offer valuable insights into the role of neuroinflammation in the development of secondary brain injury after ICH, and whether this can be therapeutically modulated. Moreover, it will help determine the feasibility and design of future phase III trials of immunomodulatory therapies in patients with ICH.

## Appendix 1

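### The primary OED t-test leaves out the three stratification factors; to the extent that they predict OED, it is conservative and less precise than it could be

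*Protocol article*

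**What the plan says.** Under Statistical methods the primary test is named outright: "For the primary analysis, we will use a two-sided independent t-test to determine a mean difference and 95% CI between the OED" on the day-7 MRI, pooled anakinra against standard care. The same kind of test is named for the exploratory comparison of high with low dose. No covariate is mentioned for either.

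Under Randomisation: "Treatment allocation will be stratified for centre of participation, admission ICH volume" (two bands, split at 30 mL), and also "renal function (estimated glomerular filtration rate (eGFR) 30–49 vs >50 mL/min/1.73 m^2". The stated purpose is "to ensure balance in factors associated with development of PHO and anakinra plasma concentrations". Nothing in the article carries these factors into the primary analysis.

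Two other statements bear on how much this matters. The Sample size calculation says "The OED is known to be independent of haematoma size, with a normal distribution". The Discussion says of OED that "it is not affected by haematoma volume and thus strongly reduces the required sample size" compared with absolute or relative PHO.

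**The concern.** Stratified randomisation makes the arms more alike on the stratification factors than chance would. If those factors predict the outcome, the treatment difference varies less from one randomisation to the next than it would under simple randomisation. The two-sample t-test does not use this. It leaves the variation between strata in its error term, so its standard error overstates the true variability, its p-value is too large on average and its confidence interval is too wide.

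Precision is what this trial has least of. Power is set at 0.80, 75 patients with 25% drop-out leave about 56 scans, and the Discussion accepts that drop-out may be higher. The stratification factors are known for every randomised patient, so any precision they offer needs no new data.

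This is not a gap that a separate analysis plan would ordinarily fill, because the protocol names a specific unadjusted test.

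**Working it through.** **Inputs from the protocol.** Control mean and SD: "we assume an OED of 0.60 (SD 0.25) at day seven in the standard care group". Anakinra mean 0.40, SD 0.25, so the difference is 0.20 cm. Ratio 1:2, alpha 0.05 (two-sided, as the test is described), power 0.80, 19 + 39 evaluable, 25% drop-out, 25 + 50 = 75 randomised. Strata: 3 centres × 2 volume bands × 2 renal bands = 12.

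**Input not in the protocol.** R-squared of OED on the stratification factors: assumed from 0 to 0.30.

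**Step 1: reproduce the plan's figure.** For 19 and 39 evaluable, SE = 0.25 × √(1/19 + 1/39) = 0.0699 and the noncentrality is 0.20/0.0699 = 2.86. With 56 df the noncentral t gives power 0.802 (0.799 at 19 and 38). The stated 19 + 39 is therefore the correct size for an unadjusted t-test. The 95% CI half-width is 0.140 cm.

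**Step 2: analytic effect of adjustment at 19 + 39.** Residual SD = 0.25 × √(1 − R²). Four more df are spent: two for centre, one for volume, one for renal function.

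| R² | Residual SD | Power, adjusted | CI half-width (cm) |
|---|---|---|---|
| 0 | 0.250 | 0.801 | 0.140 |
| 0.05 | 0.244 | 0.821 | 0.137 |
| 0.10 | 0.237 | 0.841 | 0.133 |
| 0.20 | 0.224 | 0.880 | 0.126 |
| 0.30 | 0.209 | 0.918 | 0.117 |

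This is slightly optimistic, because it takes the covariates as balanced between the groups analysed.

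**Step 3: simulation with sparse strata and missing scans.** 75 patients were randomised 1:1:1 within the 12 strata in permuted blocks. A random 25% were removed (75 × 0.75 = 56.25 left on average). OED was then analysed by t-test and by a linear model with treatment, centre, volume band and renal band. Assumptions: centre shares 50/25/25%, 45% above 30 mL, 10% in the low-eGFR band; the explained variance split half to volume, a quarter to centre and a quarter to renal function. Type I error used 10,000 runs each for block sizes 3 and 6; power used 4,000 runs with block size 3.

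| R² | Type I error, t-test | Type I error, adjusted | Power, t-test | Power, adjusted | Half-width, t-test / adjusted (cm) |
|---|---|---|---|---|---|
| 0 | 0.049–0.050 | 0.048–0.052 | 0.79 | 0.77 | 0.142 / 0.144 |
| 0.10 | 0.043–0.049 | 0.052 | 0.79 | 0.82 | 0.142 / 0.137 |
| 0.20 | 0.035–0.038 | 0.045–0.054 | 0.80 | 0.85 | 0.142 / 0.129 |
| 0.30 | 0.032–0.035 | 0.051–0.053 | 0.81 | 0.90 | 0.142 / 0.121 |

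Ranges are over the two block sizes. Monte Carlo standard error is about 0.002 for type I error, √(0.05 × 0.95/10,000), and 0.006 for power, √(0.8 × 0.2/4,000).

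**Reading.** As R² rises the t-test's power stays near 0.80 while its type I error falls below 5%. The adjusted model holds about 5% and turns the explained variance into power. At R² = 0 the adjusted model loses between 1 and 2 points (0.7855 to 0.7720).

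**The case against.** The best reply is that the factors may not predict this outcome. The protocol says twice that OED does not depend on haematoma size; on that premise the volume band carries no information about it. The Randomisation section gives plasma concentration as a second reason for stratifying. It does not assign reasons factor by factor, but renal function could be there for that reason and would then say little about OED in untreated controls. That might leave mainly centre. At R² = 0 nothing is lost by the t-test and adjustment costs a little. This stands, and it is why the loss has to be stated conditionally. It does not remove the point: the same section cites association with PHO as a reason for stratifying, OED is the trial's measure of PHO, and the downside of adjusting is small.

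Three stronger readings are tempting and are not supported.

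- **That the p-value and interval are invalid.** At worst the interval over-covers; false positives are not inflated.
- **That the sample size is undermined.** It was computed for this t-test, and the simulated power of that test does not fall as R² rises.
- **That type I error drops to 3.9% or 2.8% at R² of 0.10 or 0.20.** Those values come from 2 × [1 − Φ(1.96/√(1 − R²))], which assumes perfect balance. With 12 strata, three arms and missing scans, simulation gives 4.3–4.9% and 3.5–3.8%.

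Nor does leaving out baseline variables that were not stratified on, such as NIHSS or ICH location, make the t-test miscalibrated. Using them would be a choice for efficiency only.

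**Conclusion.** The point holds as a matter of efficiency and of matching the analysis to the randomisation; it is not an error of validity. The primary test ignores three factors that the trial stratifies by, and to the extent that they predict OED it is conservative and imprecise. In simulation the power forgone is about 2, 5 and 9 points at R² of 0.10, 0.20 and 0.30 (0.7915 to 0.8153, 0.8013 to 0.8538, 0.8113 to 0.9025), and nothing at R² = 0.

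The direction is firm and the size is not. It rests on assumed R-squared values, stratum frequencies and block sizes, on scans missing at random, and on a variance split that gives half the weight to volume, the factor that the protocol itself says does not matter for OED.

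**What to change.** Before database lock, and without sight of outcome by arm, replace the primary t-test with a linear model of day-7 OED on treatment and the stratification factors: centre, admission ICH volume and renal function. State a rule for pooling sparse levels that does not use allocation or outcome. The primary estimate is the pooled-anakinra-minus-control contrast with its 95% CI, still a mean difference in cm. Take the exploratory high-minus-low contrast from the same model by fitting treatment with three levels. Keep the t-test as a sensitivity analysis.

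Do not add onset-to-MRI time. It is measured after randomisation, and the timing of the scan may depend on clinical course.

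Cost: a change of wording and no new data. The stratification factors take four degrees of freedom and the separate dose term one more. If the factors do not predict OED, the loss is up to about 2 points of power.

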^ Recombinant human IL-1ra (anakinra) has been available for treatment of inflammatory disease such as rheumatoid arthritis since 2001. Preclinical data support a neuroprotective therapeutic potential of anakinra in both ischaemic and haemorrhagic stroke. In a meta-analysis of preclinical stroke studies, IL-1ra treatment reduced infarct volume by 36% in rodents.^
20
^ To date, two clinical studies have investigated the use of anakinra in patients with acute stroke.^21,22^ Both trials indicated a significant reduction of serum inflammatory markers without safety concerns.^21,22^ Amongst the 119 participants, only five patients with ICH were included in these two trials.^
21
^ Recently, a first randomised trial testing anakinra in 25 patients with spontaneous ICH was published (BLOC-ICH).^
23
^ They could demonstrate feasibility of anakinra treatment within 8 h after ICH onset but were unable to determine the effect on PHO formation due to limited sample size. Hence, the effect of anakinra on perihematomal inflammation after spontaneous ICH and the development of secondary brain injury remains unclear.

The Anakinra in Cerebral haemorrhage to Target secondary Injury resulting frOm Neuroinflammation (ACTION) trial aims to establish whether administration of anakinra in patients with ICH affects PHO formation. We hypothesise that anakinra safely reduces PHO after ICH, and that its effect is dose-dependent.

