## Methods

### Trial design

ACTION (www.action-study.nl) is an investigator-initiated, phase II, prospective, randomised trial with open label treatment and blinded end-point assessment (PROBE). There will be three arms (1:1:1). In the first arm, participants will receive a high-dose of intravenous anakinra in addition to standard medical management, in the second arm, a subcutaneous low-dose of anakinra in addition to standard medical management, and the third arm constitutes of standard medical management without anakinra. Patients in all arms will get standard medical management. Each treatment arm will include 25 patients. The primary aim of the trial is to study whether use of anakinra has an effect of PHO compared to standard medical management; for this analysis we will combine the two anakinra treatment arms. In the secondary analysis we will investigate whether a difference in dosage of anakinra modifies the effect of anakinra on PHO. Main reasons for studying whether such a difference exists, is that the subcutaneous administration of anakinra is easier in use and has lower costs than the intravenous administration, which on the other hand might be more effective.

The study will be conducted according to the principles of the Declaration of Helsinki and in accordance with the Medical Research Involving Human Subjects Act (WMO). The study was approved by the medical ethics committee of the region Arnhem-Nijmegen (reference NL76607.091.21).

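### The primary t-test merges the two anakinra arms, so any dose effect counts as random error and makes the 95% CI conservative; whether power suffers depends on which SD the planned 0.25 is

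*Protocol article*

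**What the plan says.** Under Trial design the protocol article randomises 1:1:1 to high-dose anakinra, low-dose anakinra and standard care. Of the primary question it says "for this analysis we will combine the two anakinra treatment arms". Under Statistical methods it names the test: "we will use a two-sided independent t-test to determine a mean difference and 95% CI between the OED at MRI on day 7". The samples compared are the "OED at MRI on day 7 ± 1 of the two anakinra treatment groups combined and the standard care group". High dose against low dose is a separate, exploratory t-test.

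The Introduction expects the two anakinra arms to differ: "We hypothesise that anakinra safely reduces PHO after ICH, and that its effect is dose-dependent". No size is given for that difference anywhere.

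The Sample size calculation states for controls: "we assume an OED of 0.60 (SD 0.25) at day seven in the standard care group". For anakinra it gives a "reduction of OED from 0.60 to 0.40 (SD 0.25) in the anakinra treated group (high and low dose groups combined". So one SD serves both the single control arm and the merged two-dose group.

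**The concern.** A two-sample t-test treats the merged anakinra patients as one homogeneous sample. Randomisation fixed how many patients receive each dose, so a difference between dose means is systematic and adds nothing to the sampling error of the average anakinra effect. The t-test still puts it into the error term. The more the dose-dependence hypothesis is true, the wider the primary interval becomes relative to what it estimates. This matters because the Discussion admits a limited sample size and wants effect sizes for phase III design.

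The SD raises a second question. If within-arm SDs were equal in all three arms and the doses differed, the merged group's SD would exceed the control SD. Giving both the value 0.25 leaves it unclear which quantity was planned.

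The point concerns only the error term and the meaning of the SD. Averaging the two doses for the primary question is not disputed.

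**Working it through.** **Inputs.** From Sample size calculation: means 0.60 and 0.40 cm, SD 0.25, two-sided α 0.05, power 0.80, ratio 1:2, evaluable patients 19 and 39. Assumed, because it is not in the document: D, the low-dose mean minus the high-dose mean, from 0 to 0.4 cm, centred on 0.40.

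**Step 1: reproduce the plan.** Control n = 1.5 × [0.25 × (1.960 + 0.842) / 0.20]² = 18.4, so 19. Exact noncentral-t power is 0.802 at 19 v 39. The stated size reproduces.

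**Step 2: variance of the merged group.** With within-arm SD σ and two nearly equal arms, merged variance ≈ σ² + D²/4. For σ = 0.25:
- D = 0.1: 0.0625 + 0.0025 = 0.0650, SD 0.255
- D = 0.2: 0.0625 + 0.0100 = 0.0725, SD 0.269
- D = 0.4: 0.0625 + 0.0400 = 0.1025, SD 0.320

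**Step 3: effect on the interval if 0.25 is the within-arm SD.** The t-test's pooled variance at D = 0.2 is (18 × 0.0625 + 38 × 0.0725) / 56 = 0.0693, SD 0.263. Against the correct 0.25 the interval is 0.263 / 0.25 = 1.05 times as wide. The same sum gives about 1.12 at D = 0.3 and 1.20 at D = 0.4.

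**Step 4: simulation**, at least 100,000 replicates per D, 19 control v 20 high + 19 low, average effect 0.20.

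*Reading A: 0.25 is the within-arm SD.*

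| D (cm) | Merged t-test power | Coverage | CI half-width (cm) |
|---|---|---|---|
| 0 | 80.2% | 95.0% | 0.140 |
| 0.1 | 80.0% | 95.3% | 0.141 |
| 0.2 | about 78% | 96.1% | 0.147 |
| 0.3 | about 75% | 97.1% | 0.156 |
| 0.4 | about 70% | 98.1% | 0.168 |

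The three-arm contrast with arm-specific variances has power of about 79.3% and coverage of 95.0% at every D. The 39 patients cannot split evenly. With the odd patient in the low-dose arm (19 high + 20 low), the t-test's power is about 76%, 71% and 65% at D = 0.2, 0.3 and 0.4, because the merged mean shifts slightly towards the low dose.

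*Reading B: 0.25 is the combined SD, as written.* The within-arm SD is then √(0.0625 − D²/4), which is 0.229 at D = 0.2 and 0.150 at D = 0.4. Power of the merged t-test is 80–85% over the whole range with the odd patient in the high-dose arm, and about 80% with that patient in the low-dose arm. The interval still over-covers:

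| D (cm) | Merged t-test coverage | Its half-width (cm) | Arm-specific contrast half-width (cm) |
|---|---|---|---|
| 0.2 | about 95.6% | 0.140 | 0.138 |
| 0.3 | 96.4% | 0.140 | 0.133 |
| 0.4 | 97.4% | 0.140 | 0.127 |

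The arm-specific contrast covers at 95.0%. A contrast with one common variance would not be safe on reading B: its coverage falls to 94.2% at D = 0.2 and 90.4% at D = 0.4, because the control SD then exceeds the anakinra within-arm SD.

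**Step 5: type I error.** With an average effect of zero, the test rejects in 100% minus the coverage. On reading A that is 3.9% at D = 0.2 and 1.9% at D = 0.4, both below 5%.

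**The case against.** The strongest reply is that the protocol attaches 0.25 to the merged group. A combined-group SD already contains any between-dose spread, so the planned test has its 80% at every D. That stands. A reader might infer from the merging that the stated power is not delivered; the document does not support this. A shortfall needs 0.25 to be a within-arm SD, which is not written, and a D near or above 0.2 cm, which is the whole assumed treatment effect.

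The larger losses are also remote. D = 0.4 means OED of 0.20 on high dose and 0.60 on low dose, so an inert low dose. The Discussion argues instead that a lower dose may suffice because the blood-brain barrier is compromised. If all 75 patients were evaluable, power at D = 0.4 would still be about 80% even on the within-arm reading.

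The text does not say whether the t-test assumes equal variances. On reading A a Welch version gives about 79% power and 95.6% coverage at D = 0.2, and about 78% power at D = 0.3. It recovers part of the loss but not all of the over-coverage.

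Finally, the planned test is simple, matches its question and errs on the safe side. All of this limits the point's weight. It does not remove the over-coverage, which appears on both readings of the SD.

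**Conclusion.** The point holds as a modest flaw in the error term. If the doses differ, the primary 95% CI is conservative: coverage is about 96% at D = 0.2 and 97–98% at D = 0.4, with almost no effect at D of 0.1 or less. The primary test remains valid, and nothing here says that the sample size is wrong.

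The power consequence is conditional. On the protocol's wording, 80% is delivered. On a within-arm reading, power is about 78%, 75% and 70% at D = 0.2, 0.3 and 0.4, and a few points lower if the odd patient falls in the low-dose arm.

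These figures rest on normal outcomes, 19 v 39 evaluable patients, an average effect of 0.20 cm and assumed values of D. This is a cheap improvement and a request for clarification.

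**What to change.** In Statistical methods, keep the pooled question and the single primary p-value, but estimate the effect as ½ high + ½ low − control from a model with three arm means. Use arm-specific variances and Satterthwaite degrees of freedom, and report the contrast with its 95% CI. In Sample size calculation, state whether 0.25 is a within-arm or a combined-group SD, and that the power refers to this contrast.

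The cost is one sentence in each section before database lock, with no extra data. The downside is power of about 79.3% instead of 80.2% if the doses do not differ. If they do, coverage is the nominal 95%, and from about D = 0.2 the interval is narrower than the merged t-test's.

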### Adverse event reporting

Adverse events (AEs) are defined as any undesirable experience occurring to a subject during the study, whether or not considered related to the administration of anakinra or other study procedures. Serious adverse events (SAEs) are AEs that result in death, are life-threatening, require hospitalisation or prolongation of existing hospitalisation, result in persistent or significant disability, are congenital anomalies or birth defects, or other important medical events, based on the judgement by the study team. All (S)AEs reported spontaneously by the subject or observed by the investigator will be recorded. Despite the excellent safety record of anakinra and the relatively high number of complications of the disease under study, we will identify the following ‘adverse events of special interest’ (AESIs) to assess participants’ tolerability to anakinra:

*Early neurological deterioration*, defined as *a* ⩾ 2 point decrease in GCS or a ⩾4 point increase in the NIHSS score sustained for at least 8 h, within the first 3 days of hospitalisation;*Infection*, categorised as urinary tract infection, pneumonia, bloodstream infection, or other infections. Infections will be diagnosed and categorised based on the Centers of Disease Control and Prevention (CDC) definitions^
29
^;*Skin injection reaction*, defined as one or more of the following: erythema, ecchymosis, inflammation, and severe pain;*Allergic reaction*, defined as an untoward reaction to anakinra developing over minutes to days after treatment initiation, and is clinically characterised by skin-mucosal, respiratory and/or cardiovascular symptoms. This does not include known side effects of anakinra;*Anaphylaxis*, which is considered when two or more of the following occur during an allergic reaction: generalised involvement of the skin-mucosal tissue, respiratory compromise, reduced blood pressure or associated symptoms, or persistent gastrointestinal symptoms;*Neutropenia*, defined as an absolute neutrophil count (ANC) <1.5 × 10^9^/L.

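### The three-arm Fisher tests of safety are worded as event counts, include reactions that controls cannot have, and leave out the combined-anakinra-versus-control contrast

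*Protocol article*

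**What the plan says.** All references are to the protocol article.

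- **Statistical methods.** For the safety profile, "we will compare the number of AESIs and urgent medical reasons for study withdrawal between the three treatment arms". The stated method is Fisher's exact test, with the arms forming the three columns of each table. The two rows are not defined, and no AESI is exempted from the three-arm test. The time window is wide: "Safety analyses will include all SAEs and AESIs up to 90 days after randomisation".
- **Adverse event reporting.** There are six AESIs: early neurological deterioration, infection, skin injection reaction, allergic reaction, anaphylaxis and neutropenia. Infection is "categorised as urinary tract infection, pneumonia, bloodstream infection, or other infections". Allergic reaction is "defined as an untoward reaction to anakinra developing over minutes to days after treatment initiation", and anaphylaxis is a condition "which is considered when two or more of the following occur during an allergic reaction". Skin injection reaction is "defined as one or more of the following: erythema, ecchymosis, inflammation, and severe pain". The same section lists four urgent reasons for withdrawal, one of which is anaphylaxis following anakinra.
- **Trial design and Intervention.** There are 25 patients per arm. Controls receive neither anakinra nor placebo. Study drug is given subcutaneously only in the low-dose arm.
- **Data and safety monitoring board section.** The stopping rule compares the proportion of participants with an urgent withdrawal reason, both anakinra arms combined against control.
- **Outcomes.** The safety profile is the first-listed secondary outcome.

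**The concern.** Three features of the stated method sit badly together.

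1. **Unit.** Fisher's test on a 2 × 3 table needs each participant to appear once, as having or not having the event. The sentence speaks of a number of AESIs. Over 90 days one patient can have several, for example a pneumonia and a urinary tract infection. If events were entered, the test would be invalid.
2. **Arm-restricted events.** Some items in the comparison are impossible in one column of the table. A test of equal risk across three arms then partly tests the definition.
3. **Contrast.** An omnibus p-value over three arms does not address whether anakinra raises risk against standard care, nor by how much.

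The trial's hypothesis is that anakinra reduces oedema safely. At stake is whether the safety table can be interpreted: a significant result could come from the definitions, and a non-significant one would say little about the excess risk not ruled out.

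**Working it through.** The article gives no figure for the safety tests, so there is none to reproduce. The only design input taken from it is 25 patients per arm. All event counts and rates below are illustrative assumptions.

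**1. Which items can occur in which arm**

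| Item | High dose (IV) | Low dose (SC) | Control |
|---|---|---|---|
| Early neurological deterioration, infection, neutropenia | possible | possible | possible |
| Allergic reaction | possible | possible | impossible by definition (a reaction to anakinra) |
| Anaphylaxis | possible | possible | impossible by definition (arises within an allergic reaction) |
| Withdrawal for anaphylaxis after anakinra | possible | possible | impossible by definition |
| Skin reaction to study-drug injection | not in practice | possible | not in practice |

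The last row is a practical restriction. The definition lists signs only and does not name the drug or the route.

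**2. How few arm-restricted events give p < 0.05**

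For counts (a, b, c) with total t and 25 per arm, the exact probability is P(a, b, c) = C(25,a)·C(25,b)·C(25,c) / C(75,t). The p-value sums P over all tables with the same t that are no more probable than the observed one.

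- (4, 0, 0): P = C(25,4)/C(75,4) = 12,650/1,215,450 = 0.0104. Only the three tables with all four events in one arm are as improbable, so p = 3 × 0.0104 = **0.031**.
- (3, 0, 0): p = 3 × 0.0341 = 0.102.
- (5, 5, 0): P = C(25,5)²/C(75,10) = 0.0034; summing all tables no more probable gives p = **0.040**.
- (4, 4, 0): p = 0.115.

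Four reactions confined to one arm, or five in each anakinra arm, are therefore enough. If an event is possible only in the subcutaneous arm, the test rejects whenever that arm has at least 4. With a true rate of 10%, 20% or 30% in that arm, the probability of rejection, P(X ≥ 4) for X ~ Binomial(25, rate), is 0.24, 0.77 or 0.97.

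**3. What the omnibus test leaves out**

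Take observed counts of 10/25, 10/25 and 5/25 for an event that every arm can have.

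- Omnibus 2 × 3 exact test: p = 0.26.
- Combined anakinra versus control: 20/50 − 5/25 = 0.40 − 0.20 = 0.20.
- Wilson 95% limits: 0.276 to 0.538 for 20/50; 0.089 to 0.391 for 5/25.
- Newcombe lower limit: 0.20 − √[(0.40 − 0.276)² + (0.391 − 0.20)²] = −0.03.
- Newcombe upper limit: 0.20 + √[(0.538 − 0.40)² + (0.20 − 0.089)²] = 0.38.

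The p-value alone would not show that an excess of up to 38 percentage points remains compatible with the data. If true risk doubles from 20% to 40% in both anakinra arms, the omnibus test rejects with probability 0.31; from 10% to 20%, 0.12.

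**4. The unit, conditional on counting events**

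In a simulation with equal true risk and 20–40% of patients affected, counting participants rejects in about 4% of runs. Entering event counts in the same table, capped at 25 per arm, rejects in 24–37% at an average of 1.5 events per affected patient and 42–63% at 2.0. With no repeat events the two are identical. These rates rest wholly on assumed event frequencies and on the event-counting reading.

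**The case against.** A reader might infer that the plan treats repeat events in one patient as independent. The article does not support that. A 2 × 3 table with three arms most naturally has participants with and without the event as its rows, because event counts supply no row without an event. The same sentence applies the same tables to withdrawal reasons, which the stopping rule counts per participant. What stands is that the AESI wording names events and no rule says otherwise.

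A reader might also infer that all AESIs are pooled into one three-arm total that differs by construction. No such total is stated. The text speaks of tables in the plural and the AESIs are defined separately, so per-type tables may be what is meant. The point about arm-restricted items does not need pooling, since it applies to each per-type table.

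Skin injection reactions are not excluded from other arms by definition. An excess under subcutaneous dosing would be a genuine tolerability finding for that regimen, so it deserves reporting; a three-arm significance test adds little to it.

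Finally, the form of safety estimates is often left to a statistical analysis plan, and this is a condensed article. The absence of an interval would not by itself be a finding. But the article does fix a method, the omnibus test, and that method can be judged against the contrast the trial uses elsewhere. Nothing says that a non-significant p-value will be taken as proof of safety, and the Discussion acknowledges the limited sample size.

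**Conclusion.** The point holds in a limited form.

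- **Firm, from the definitions:** allergic reaction, anaphylaxis and the anaphylaxis withdrawal reason cannot occur in controls, so a three-arm test of these partly reflects how they are defined. For study-drug skin injection reactions the same holds in practice. The p-values of 0.031 and 0.040 depend only on 25 patients per arm and the illustrative counts.
- **Firm, from the stated method:** the omnibus test does not give the combined-anakinra-versus-control comparison that the primary analysis and the stopping rule use. The −3 to +38 point interval illustrates what is lost.
- **Conditional:** the unit is worded as events. An independence error would follow only if events were actually entered, and its size cannot be derived from the article.

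This concerns a secondary safety analysis. The primary outcome and the stopping rule are unaffected. It should be corrected before the analysis.

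**What to change.** Replace the safety-test wording along these lines:

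1. The unit is the participant with at least one event, separately for each AESI type.
2. For early neurological deterioration, infection, neutropenia and urgent withdrawal reasons (without the item for anaphylaxis after anakinra), report the risk difference with 95% CI for combined anakinra versus control, then for each dose versus control.
3. Report event counts, allergic reactions, anaphylaxis and injection-site reactions descriptively by arm. Leave the anakinra-defined reactions out of any three-arm test.

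The cost is a change of wording and a small amount of extra analysis; no new data are needed. Intervals will be wide with 25 per arm, and the report should say so.
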